### Criteria for discontinuing or modifying allocated interventions {11b}

If the patient is not suitable for DIBH, the standard clinical workflow for free breathing (FB) is followed. The patient will complete the patient experience questionnaire and progress to treatment with free breathing using no breath hold management system and with no further study interventions.

Patients are entitled to withdraw consent at any time and will revert to standard of care treatment with RPM/RGSC. Outcome data for these patients will still be collected.

### Strategies to improve adherence to interventions {11c}

Not applicable. Assessment of ease of use of treatment with the Breathe Well device is the aim of this trial, so non-adherence to the intervention should be recorded. Inability to carry out DIBH will result in free-breathing treatment as per current standard of care.

### Relevant concomitant care permitted or prohibited during the trial {11d}

No restrictions on concomitant care being offered as per standard hospital practice.

### Provisions for post-trial care {30}

Participants will receive post-treatment care as per standard hospital procedure. Compensation could be available through sponsor insurance.

### Outcomes {12}

Primary outcome:

Treatment accuracy: the specific measurement made will be the average chest wall position extracted from the EPID images captured at each treatment fraction. The metric used for analysis will be the ‘displacement’ or difference between this measured position on each captured image frame and the planned average chest wall position from the digitally reconstructed radiograph (DRR). The average per fraction displacements will be compared across the two arms of the trial.

Secondary outcomes:Setup time: The appointment duration will be measured as the time recorded in the ARIA patient management system between patient check-in and appointment end for each treatment fraction, and aggregated for each arm of the trial.Patient comfort and user friendliness. A patient survey (see Supplementary Materials) will be delivered at the timepoints indicated in the “Participant timeline {13}” section and Fig. 3: after simulation, and at the end of the first and last weeks of treatment.Technology assessment: A staff survey (see Supplementary Materials) will be delivered at the timepoints indicated in Fig. 3: after 5 and 10 sessions using Breathe Well at CT simulation and after 5 and 20 sessions using Breathe Well at treatment.To develop — offline — the use of the electronic portal imaging device (EPID) for real-time MLC tracking during monitoring the chest wall position in breast radiotherapy. This work will be reported as future research outputs.Estimated dose delivered. Measured chest wall displacement relative to planned position (taken from the EPID images captured at treatment time, see the primary outcome) will be used to apply an isocentre shift in the treatment planning system, following the approach of Doebrich et al. [13]. Hence the delivered dose will be estimated for each patient during each treatment fraction and aggregated for each arm of the trial.

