### Sample size {14}

The sample size was estimated by assuming that the systematic error in treatment accuracy, Σ, will be smaller for patients on the experimental (Breathe Well) arm than the control (RPM) arm. Previously published data for a different surface monitoring system (AlignRT: VisionRT, London, UK) is given by Kanphet et al. [14] who found a systematic error of 0.46 mm in the vertical direction. For comparison, Lutz et al. [15] found a systematic error of 1.33 mm with RPM. Assuming this study will recruit a comparable patient cohort, that any differences in treatment technique will not affect the target motion, and assuming normal distribution of the systematic error in both arms of the trial and independence of the two arms, the F-test for equality of two variances estimates 36 patients will be needed for statistical significance with a power of 0.8 and alpha error probability of 0.05. The sample size for this study was set at 40 to account for an estimated 10% dropout rate for patients who cannot maintain a breath hold and are treated with free breathing.

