## Statistical methods

### Statistical methods for primary and secondary outcomes {20a}

Primary outcome:

Treatment accuracy: a generalized estimating equation model with exchangeable correlation structure which adjusts for repeated measurements within individuals will be used to test the per fraction average chest wall displacements for all patients on each arm, testing for superiority (smaller chest wall displacement) of the Breathe Well arm compared to the RPM arm. No covariate adjustment, subgroup or sensitivity analysis is planned.

Secondary outcomes:

1. Setup time: Median and range of the appointment time will be reported for each arm. No statistical analysis is planned as clinically significant variation in the appointment time is highly dependent on hospital procedures and workflow.

2. Patient comfort and user friendliness and 3. Technology assessment: The questionnaire tools used for secondary aims 2 and 3 are not validated tools so will only be used for qualitative analysis. The median and range response scores will be reported for each arm for each question.

5. Estimated dose delivered: If the primary outcome shows superiority of the Breathe Well arm in treatment accuracy, the same model will be used to test for superiority (smaller dose differences) of the dose distributions between the Breathe Well arm and the RPM arm. If not, a qualitative analysis will be carried out identifying any patient anatomy- and treatment planning-related points of interest.

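### The primary outcome does not say whether displacement keeps its sign; read literally, the planned GEE cannot see the effect the trial was sized on, and on neither reading is 80% the power of the primary test

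*Protocol article*

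**What the plan says.** All references are to the protocol article.

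- **Outcomes {12}, primary outcome.** The metric, called displacement, is the "difference between this measured position on each captured image frame and the planned average chest wall position from the digitally reconstructed radiograph (DRR"). It is then summarised: "The average per fraction displacements will be compared across the two arms of the trial". Neither absolute value, magnitude nor root mean square is mentioned, and neither is sign.
- **Outcomes {12}, estimated dose.** The same measured displacement "will be used to apply an isocentre shift in the treatment planning system", which needs a direction.
- **Statistical methods {20a}.** The per-fraction averages go into "a generalized estimating equation model with exchangeable correlation structure which adjusts for repeated measurements within individuals", "testing for superiority (smaller chest wall displacement) of the Breathe Well arm compared to the RPM arm". The section adds: "No covariate adjustment, subgroup or sensitivity analysis is planned".
- **Sample size {14}.** The number of patients is obtained by "assuming that the systematic error in treatment accuracy", Σ, is smaller with Breathe Well. For surface monitoring it takes a "systematic error of 0.46 mm in the vertical direction", and for RPM 1.33 mm. Both arms are assumed normal. The test is an F-test for equality of two variances with power 0.8 and alpha 0.05, giving 36 patients, raised to 40 for 10% dropout. No difference in means is given.

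**The concern.** Three sections that should describe one quantity do not fit together. Sample size {14} expects the arms to differ in the spread of patient errors. Statistical methods {20a} compares means. Outcomes {12}, which should link the two, leaves open whether the averaged quantity is a position error with a sign or a distance.

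The choice decides what the trial tests. A difference between two positions is, on its face, signed. Averaged over patients, an error of +1 mm and one of −1 mm give zero, so an inaccurate arm can have the same mean as an accurate one. On that scale smaller can also mean more negative. On a magnitude scale, a wider spread does raise the mean, and the GEE can detect it.

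The trial is unblinded and plans no sensitivity analysis, so no second metric is specified. If the convention is settled after the images have been read, the primary result is open to a choice made with the data in view.

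**Working it through.** **Inputs from the protocol article.** Σ = 0.46 mm (surface monitoring) and 1.33 mm (RPM), normal, 1:1 allocation, 36 evaluable patients (18 per arm), power 0.8, alpha 0.05, 10% dropout.

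**Assumptions, not in the article.** Arm means equal (zero) unless stated; 15 fractions (range 5 to 25); SD of the fraction averages within a patient, σ, from 0 to 2 mm.

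**1. The plan's own figure.** The variance ratio is (1.33/0.46)² = 8.36. Exact F-test power:

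| Patients per arm | One-sided | Two-sided |
|---|---|---|
| 8 | 84.1% | 74.4% |
| 9 | 88.5% | 80.6% |
| 18 | 99.5% | 98.8% |

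The stated inputs therefore need 16 patients in total (one-sided) or 18 (two-sided), and 36 does not reproduce. The dropout step does: 36/0.9 = 40. The point here is that this power, whatever its value, belongs to a variance test that {20a} does not plan.

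**2. Signed reading.** With no covariates and equal numbers of fractions, an exchangeable GEE compares the arm averages of the patient means. At σ = 0 the standard error of the difference is √[(0.46² + 1.33²)/18] = √(1.9805/18) = 0.33 mm. The expected difference is 0 when the arm means are equal, whatever the two SDs are. In 20,000 simulated trials per setting (Welch t on patient means), two-sided rejection was about 5% for every σ from 0 to 2 mm and for 5, 15 or 25 fractions. An uncorrected robust z test gave 6–7%. This is the type I error rate.

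**3. Signed reading with an offset** (15 fractions, σ = 1 mm, one-sided 5% test for a smaller Breathe Well value; the 1 mm offsets are illustrations):

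| Offset | Signed: Breathe Well called superior | Absolute: Breathe Well called superior |
|---|---|---|
| Breathe Well −1 mm | 88% | 11% |
| RPM −1 mm | 0% | 99% |

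In the second row RPM is worse in both bias and spread, and the signed test still never favours Breathe Well.

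**4. Magnitude reading.** For a normal error with mean zero, E|X| = √(2/π) × SD, and the SD of a fraction average is √(Σ² + σ²).

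- σ = 0: 0.798 × 0.46 = 0.37 mm v 0.798 × 1.33 = 1.06 mm, difference 0.69 mm.
- σ = 1: 0.798 × √1.2116 = 0.88 mm v 0.798 × √2.7689 = 1.33 mm, difference 0.45 mm.
- σ = 2: 0.798 × √4.2116 = 1.64 mm v 0.798 × √5.7689 = 1.92 mm, difference 0.28 mm.

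Power with 18 per arm (two-sided Welch t on patient means of the absolute fraction averages):

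| Fractions (assumed) | σ = 0 | 0.5 mm | 1.0 mm | 1.5 mm | 2.0 mm |
|---|---|---|---|---|---|
| 5 | 96% | 92% | 70% | 40% | 21% |
| 15 | 96% | 95% | 86% | 65% | 42% |
| 25 | 96% | 95% | 89% | 75% | 54% |

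**5. Where the cancellation happens.** Σ is a between-patient quantity. It survives averaging over frames and fractions within a patient, and cancels only when patients are averaged into an arm mean. Averaging frames within a fraction removes only opposite-signed variation inside that fraction. The calculation has no frame-level input, so it puts no number on that part. For the same reason the powers in step 4 are for the absolute value of the fraction average, not for a per-frame absolute value.

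**The case against.** The strongest reply is that the article never calls the outcome signed. Statistical methods {20a} describes superiority as smaller displacement and the hypothesis is about accuracy; both make sense only for a magnitude. The isocentre shift belongs to a secondary outcome: it shows that the raw measurement has a direction, not that the primary summary keeps it. On the magnitude reading the planned GEE can detect the sizing effect, with power above 80% when random error is modest. A condensed article may also leave such conventions to a fuller document.

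Much of this stands. A reader might infer that the primary outcome is definitely signed and that the test has no power. The article does not support that: the sign convention is undefined, and about 5% rejection holds only for signed values with equal arm means. A signed comparison would detect a true mean offset, in about 79% of trials two-sided at 1 mm (15 fractions, σ = 1 mm). A reader might also conclude that Breathe Well is likely to be declared superior falsely. The 88% figure rests on an assumed 1 mm offset and a one-sided test, and the article gives neither.

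The reply does not remove the point. The article sets out a metric, a model and a direction, and its literal wording gives a test that cannot see the difference in spread used for sizing. Even if a magnitude is meant, it is not said whether the absolute value is taken per frame or after averaging the fraction. Those are different outcomes: the second hides movement around the planned position, although the primary hypothesis concerns maintaining chest position. Nor does the magnitude reading rescue the stated power, because {14} considers no random error.

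**Conclusion.** The point holds as an undefined sign convention in the primary outcome, joined to a sample size that rests on a different quantity. Under the plan's sizing values with 18 per arm, the literal signed reading gives about 5% rejection if the arm means are equal. The magnitude reading gives about 96% to 42% for σ of 0 to 2 mm with 15 fractions, and down to 21% with 5 fractions. On neither reading is the stated 80% the power of the primary test. The fraction numbers, the σ values and the equal means are assumptions; the two Σ values and the 18 per arm come from the article. The range between readings is wide enough that the definition should be fixed before the arms are compared.

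**What to change.** - **Outcomes {12} and Statistical methods {20a}.** Define the per-fraction outcome as the mean absolute (or root-mean-square) displacement from the DRR position, taken on each frame before averaging over the fraction. Run the GEE on that value, and state the sidedness of the test.
- **Secondary descriptions.** Report the signed mean (bias) and the between-patient SD of signed patient means (Σ) by arm. Add a comparison of variances (F-test or Brown–Forsythe) to match the assumption in {14}. Use signed values for these and for the isocentre shift, not for the primary test.
- **Sample size {14}.** Restate the power for the primary quantity, with stated values for random error and number of fractions, and show a range if they are uncertain.

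**Cost.** A change of wording and a new power calculation, using the same images and patients. The absolute value is skewed and includes random error, so the restated power may be less favourable than 80%.

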### Participant timeline {13}

Table 1 shows the schedule of enrolment, interventions, and assessments. Initial toxicity baseline will be taken at enrolment, and again at post-treatment follow-up at 6 weeks and every 6 months for three visits.

**Table 1 Tab1:**
[figure not shown]
Schedule of enrolment, interventions, and assessments

### Sample size {14}

The sample size was estimated by assuming that the systematic error in treatment accuracy, Σ, will be smaller for patients on the experimental (Breathe Well) arm than the control (RPM) arm. Previously published data for a different surface monitoring system (AlignRT: VisionRT, London, UK) is given by Kanphet et al. [14] who found a systematic error of 0.46 mm in the vertical direction. For comparison, Lutz et al. [15] found a systematic error of 1.33 mm with RPM. Assuming this study will recruit a comparable patient cohort, that any differences in treatment technique will not affect the target motion, and assuming normal distribution of the systematic error in both arms of the trial and independence of the two arms, the F-test for equality of two variances estimates 36 patients will be needed for statistical significance with a power of 0.8 and alpha error probability of 0.05. The sample size for this study was set at 40 to account for an estimated 10% dropout rate for patients who cannot maintain a breath hold and are treated with free breathing.

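### The 36 patients stated for 80% power do not follow from the stated inputs, and the F-test they size is not the trial's primary test

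*Protocol article*

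**What the plan says.** Sample size {14} sizes the trial on the systematic error Σ. For a different surface-monitoring system it cites a study that "found a systematic error of 0.46 mm in the vertical direction", and for the control system one that "found a systematic error of 1.33 mm with RPM". It assumes that the systematic error is normal in both arms and that the arms are independent, and sets an "alpha error probability of 0.05". It concludes that "the F-test for equality of two variances estimates 36 patients will be needed for statistical significance with a power of 0.8". Enrolment is then raised to 40 for 10% dropout. Sidedness is not stated.

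The primary analysis in {20a} is "a generalized estimating equation model with exchangeable correlation structure which adjusts for repeated measurements within individuals". It is applied to the average chest wall displacement at each fraction, and superiority means smaller displacement with Breathe Well. The same section plans no variance comparison and no sensitivity analysis.

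**The concern.** There are two faults. First, the section gives every input that a two-variance F-test needs, and a ratio of nearly three between the standard deviations is large for such a test. Eighteen patients per arm looks like far more than 80% power would require. Second, the test used for sizing compares spread between patients, while the test used for the conclusion compares average displacement. Power for one says nothing direct about the other.

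This section is the article's only justification for the trial's size. A reader who takes 80% as the power of the primary comparison has no sound basis for interpreting a null result. The primary test also gates the dose analysis, because {20a} tests dose formally only if the primary outcome shows superiority.

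**Working it through.** **Inputs.** Σ = 0.46 and 1.33 mm, alpha 0.05, power 0.80, normality and independent arms, all from {14}. Allocation is 1:1, from {16a}. The 40 patients are the total for two equal groups (Abstract, {16a}), so 36 is also a total, 18 per arm. Σ is read as a standard deviation because it is given in mm and enters a test of variances.

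**The plan's own figures.** The dropout step reproduces: 36/(1 − 0.10) = 40. The 36 does not, as shown next.

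**F-test.** R = (1.33/0.46)² = 2.891² = 8.36. With n per arm and F on (n − 1, n − 1) degrees of freedom:

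- two-sided power = P(F > F₀.₉₇₅/R) + P(F < F₀.₀₂₅/R)
- one-sided power = P(F > F₀.₉₅/R)

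For example, at n = 9 two-sided, F₀.₉₇₅(8, 8) = 4.433 and 4.433/8.36 = 0.530, which gives power 0.806.

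| n per arm | Total | Two-sided power | One-sided power |
|---|---|---|---|
| 7 | 14 | 0.665 | 0.782 |
| 8 | 16 | 0.743 | **0.841** |
| 9 | 18 | **0.806** | 0.885 |
| 18 | 36 | 0.988 | 0.995 |

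The smallest sizes that reach 80% are 18 in total two-sided and 16 one-sided.

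**Could another reading give 36?**

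- Standard deviations entered as variances (R = 2.891): 30 per arm two-sided (60 in total) or 24 one-sided (48). At 18 per arm the power is 0.563 or 0.688.
- 36 read as a per-arm number: this conflicts with 40 as the total for both arms, and F-test power at 36 per arm is essentially 1 with R = 8.36.
- A one-sided comparison of means that treats 1.33 − 0.46 = 0.87 mm as a mean difference, with root-mean-square SD 0.995: 34 in total. This is close, but it is not the F-test and it uses standard deviations as means.

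None of the F-test variants tried at alpha 0.05 and power 0.80 gives 36. The figure is exactly twice the two-sided total of 18, so a total may have been taken as a per-arm number. That is a guess, and nothing below depends on it.

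**What 18 per arm detects with 80% power.** The variance ratio is 4.05 two-sided or 3.44 one-sided. Against 1.33 mm this means a Breathe Well Σ of 1.33/√4.05 = 0.66 mm or 1.33/√3.44 = 0.72 mm, not 0.46 mm.

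**Power of the primary GEE (illustration only).** The article gives no mean difference, between-fraction SD or number of fractions, and does not say whether displacement is signed or absolute. The simulations assume 18 per arm, patient means normal about zero with SD 0.46 or 1.33 mm, normal fraction-to-fraction noise, and analysis of absolute displacement. With equal fractions per patient, the GEE contrast is the difference between arms in patient means.

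| Fractions (assumed) | Test | SD 1 mm | SD 1.5 mm | SD 2 mm |
|---|---|---|---|---|
| 15 | two-sided, small-sample reference | 87% | 66% | 43% |
| 15 | one-sided, robust SE, normal cut-off | 96% | 83% | 62% |
| 25 | one-sided, robust SE, normal cut-off | 97% | 90% | 73% |
| 5 | one-sided, robust SE, normal cut-off | 85% | 59% | 38% |

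SD is the assumed between-fraction SD. With no fraction-level noise, two-sided power is about 96%. If signed displacement is analysed, rejection stays at about 5%, the alpha level, because a difference in spread about zero produces no difference in means.

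**The case against.** The strongest reply is that the arithmetic error is conservative: on the stated inputs 36 is twice what the F-test needs, so the enrolment of 40 is not undermined. That is true, and it is why no change in number is asked for. It does not make the sentence correct, since 36 patients and 80% power cannot both go with 0.46 and 1.33 mm.

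A second reply is that the two tests are not wholly disconnected. If displacement is taken as an absolute value, a smaller Σ does imply a smaller mean displacement. This also stands, but the power then depends on fraction-level noise and on the number of fractions, neither of which enters the calculation.

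A third is that the GEE powers above rest on assumed inputs and shift with sidedness, number of fractions and the sign convention. This is correct. They show that the power is undetermined and should not be read as evidence that the trial is underpowered.

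Finally, a separate analysis plan may give the GEE power. That would not mend the article, which states both the sizing test and the primary test itself.

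**Conclusion.** The concern holds on both counts. On the stated inputs, 80% power by the F-test needs 18 patients in total two-sided or 16 one-sided, and the stated 36 gives 98.8% or 99.5%. This rests on Σ being a standard deviation; treating it as a variance gives 60 or 48, which also misses 36. The F-test is not the primary test, so the stated 0.8 is not the trial's power for its own primary hypothesis. That power may lie above or below 80%, and the article does not give what is needed to say which.

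**What to change.** Keep the 40 patients and rewrite {14} in two parts.

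1. Correct the F-test statement and name its sidedness. Either 18 patients in total (two-sided) give 80% power for 0.46 versus 1.33 mm, or 36 evaluable patients give about 99%. Equivalently, 36 give 80% power for 0.66 versus 1.33 mm two-sided, or 0.72 versus 1.33 mm one-sided.
2. Add the power of the primary GEE at 36 evaluable patients and present that as the trial's power. State the sidedness, the number of fractions, whether displacement is signed or absolute, and a range of between-fraction SD.

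The cost is a short recalculation and a few sentences, with no further patients. The power reported for the primary analysis may turn out lower than 0.8.

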### Recruitment {15}

Patients suitable for inclusion will be identified by the breast cancer multi-disciplinary team clinicians. Participation in the trial will be offered to the patient by their consulting radiation oncologist and consent will be taken by delegated staff at the hospital.

Recruitment rate is expected to be relatively high due to the non-invasive nature of the intervention proposed, the fact that no extra appointments are required and no extra radiation dose will be delivered, and the number of eligible patients treated at the site.

